## Abstract

Parkinson’s disease (PD) is a progressive neurological disorder that often leads to gait impairments and an increased risk of falls, negatively impacting quality of life. Inertial-based wearables have extended gait evaluation beyond clinical settings, but their technical integration and general accessibility hinder widespread adoption. Smartphones, equipped with inertial sensors, present a scalable approach for gait assessment and retraining/rehabilitation. Auditory cueing, specifically music, has shown promise to retrain gait, yet its use and uptake is often limited by a lack of personalisation. This paper outlines an exploratory and experimental protocol to evaluate CuePD, a smartphone application/app that delivers near real-time gait assessment and personalised auditory cues (including music) for gait retraining in people with PD (PwPD). The protocol characterises beneficial and non-beneficial responses to different cueing strategies and presents separate analysis for the technical validation and gait response outcomes to reduce interpretive ambiguity between measurement performance and behavioural effects. Specifically, the protocol presents: 1) validation of CuePD’s spatio-temporal gait characteristics in a controlled laboratory setting; 2) process to understand the usefulness of various auditory cues (metronome beats, instrumental music, and vocal music) to improve gait stability (i.e., increase gait speed and stride length while reducing gait variability); 3) evaluation of acceptance and preference of PwPD for personalised music cues; and 4) relationship between PwPD's musicality and their ability to adhere to auditory cues. Findings from the study will inform the suitability of gait retraining via smartphone-based app technology, personalised to the individual. Personalisation (gait characteristics and music) may potentially encourage long-term engagement for gait retraining which could lead to reduce falls and improved quality of life for PwPD. By explicitly accounting for individual variability, this protocol aims to clarify for whom and under what conditions auditory cueing is appropriate. Future work should systematically evaluate this approach as responses to auditory and/or music-based cueing in PwPD are heterogeneous with possible neutral or adverse effects, e.g., cognitive overload or exacerbation of freezing. This trial is registered at ClinicalTrials.gov (NCT06941779).

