#### Reference standard.

The reference for this study is Opal (https://clario.com/solutions/precision-motion-for-research/) which interfaces with Mobility Lab, a validated commercially available system that enables comprehensive gait assessment [22]. It allows for the wireless synchronisation of up to six IMUs (Opal V1), which incorporate tri-axial accelerometers (range:  ±  16g and  ±  200g), gyroscopes (range:  ±  2000°/s), and magnetometers (range:  ±  8 Gauss). During each walking task, a single Opal IMU (26g, 50 × 40 × 14 mm), sampling data at 128 Hertz/Hz, will be attached to the talus joint of each foot of the participant. Reference standard data will be used to validate CuePD’s temporal, spatial, and spatiotemporal gait characteristics (inc. asymmetry and variation) in PwPD to ensure primary outcomes are robust.

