### Outcome measures

#### Validation of gait characteristics.

This assesses the validity of CuePD to quantify PwPD gait characteristics against an established gold/reference-standard wearable (Opal). Gait characteristics include the mean, variability and asymmetry of temporal, spatial, and spatiotemporal characteristics (i.e., step time, stride time, stance time, swing time, stride length). Establishing the validity of CuePD in measuring gait characteristics is essential to accurately detect changes before and after cueing and to precisely tailor the administered cues to each individual’s physiological condition.

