### Statistical analysis

For the first primary objective, all gait characteristics derived from CuePD and reference will be compared using ICC_2,1_ (absolute agreement), a two-way random-effects model for single measures that evaluate the absolute agreement between raters. The level of agreement will be interpreted as: < 0.5 shows poor agreement, 0.5–0.75 moderate, 0.75–0.9 good and 0.9–1.0 excellent. PCC’s will be calculated to measure the linear correlation between the two sets of results. Correlation coefficients will be interpreted as follows: zero (0), weak (±0.1 to ±0.3), moderate (±0.4 to ±0.6), strong (±0.7 to ±0.9), and excellent/perfect (+1 or −1).

The median, mean, standard deviation (SD), minimum/min, maximum/max, and standardised response mean (SRM) of cadence, stride length, gait speed and CV_stride-time_ will be calculated. These descriptive statistics will provide context for interpreting changes and help to clarify the magnitude and consistency of cueing effects. SRM allows for assessment of responsiveness and comparison of results to other studies. The SRM will be interpreted as: > 0.8 large positive response, 0.5–0.8 moderate responsiveness, and <0.5 low responsiveness where positive values imply an improvement for cadence, gait speed and stride length but negative is an improvement for CV_stride-time_, i.e., reduces variability.

To evaluate the cueing modality adherence, the percentage change in cadence from the baseline walk to each cueing modality will be calculated for each participant. The most effective cueing modality will be identified as the one producing a change closest to 10%.

Model assumptions will be formally checked, where residual normality and normality of gait characteristics within each cue condition will be assessed using the Shapiro-Wilk test, and sphericity with Mauchly’s test. The Greenhouse-Geisser correction will be applied if sphericity is violated.

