A two-way mixed ANOVA will be used to assesses the effects of cueing modality and walk order on outcomes, i.e., cadence, gait speed, stride length, and CV_stride-time_. Comparable to the referenced PD study, cueing modality will be modelled as a within-subject factor, while walk order as a between-subject factor to account for potential sequence effects. For each outcome, within-participant changes from baseline will be calculated using cue-specific difference scores. To account for differences in scale and statistical distribution among the outcomes, change scores will be computed using Equations (30)-(31):

Percentage change of gait speed and stride length from baseline, calculated as:

$$\%\Delta =\frac{\text{Cue Value}-\text{Baseline Value}}{\text{Baseline Value}}\times \text{1}\text{0}\text{0}$$
(30)

In contrast,${\text{ CV}}_{\text{stride}-\text{time}}$, a dimensionless ratio-based variable that may have a skewed distribution, change will be computed using the natural log-ratio of cue value to baseline:

$$\Delta_{log}=\text{log}\left(\text{Cue Value}+\in \right)-\text{log}\left(\text{Baseline Value}+\in \right)$$
(31)

where 𝜖 is a small constant to avoid the logarithm of zero. This transformation was chosen as ${\text{CV}}_{\text{stride}-\text{time}}$ is a ratio-based measure that can be highly skewed and exhibit unequal variances across conditions. Applying the *log* transformation to change scores helps to normalise the distribution and stabilise the variance, thereby supporting more reliable statistical comparisons of cueing effects on ${\text{CV}}_{\text{stride}-\text{time}}$ in this within-subjects design. Post-hoc comparisons between cueing modalities will be conducted using paired t-tests, with Bonferroni correction applied to account for multiple comparisons. Effect sizes will be reported using Cohen’s d.

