### Primary objectives: Validity and evaluating the effects of personalised auditory cues on gait

The impact each personalised auditory cue has on participants’ stride length, gait speed, and${\text{ CV}}_{\text{stride}-\text{time}}$ are a significant exploratory interest. These metrics, in particular${\text{ CV}}_{\text{stride}-\text{time}}$, where a decrease is known to reduce the risk of falling, have indicated variable effects among PwPD in other cueing-related studies, particularly where music cueing is not personalised [9,44,73]. The findings from this study will establish a baseline understanding of their (i) validity (from an app and smartphone worn on the lower back) and (ii) whether personalised cues can consistently reduce stride variability across a broader range of participants.

Observed gait responses will be interpreted in the context of sequence-conditional effects (cue order, exposure, and adaptation over time), and not as definitive evidence of causal superiority of one cueing condition over another. Analyses of gait variability and asymmetry will be interpreted cautiously, as these measures typically exhibit greater dispersion and may be underpowered (as sample size of based on gait speed). Emphasis will be placed on estimating effect sizes and examining consistency of responses across conditions, rather than on formal hypothesis testing.

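### The device behind the cue-effect outcomes is never named; the text implies the app under validation, while the reference data from each walk are assigned only to validation

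*Protocol article*

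**What the plan says.** The Abstract states that the protocol "presents separate analysis for the technical validation and gait response outcomes to reduce interpretive ambiguity between measurement performance and behavioural effects".

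Under Reference standard, the Opal sensors are worn on each foot: "During each walking task, a single Opal IMU" is attached per foot, sampling at 128 Hz. The stated use of the data follows: "Reference standard data will be used to validate CuePD", and the purpose given is "to ensure primary outcomes are robust". No other use of the Opal data is stated anywhere.

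Under Validation of gait characteristics, the validity of CuePD "is essential to accurately detect changes before and after cueing"; the same sentence adds that it is also needed for tailoring the cues.

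In the Discussion section on the primary objectives, stride length, gait speed and CV stride-time are named as the cue-response measures. The text then refers to their "validity (from an app and smartphone worn on the lower back".

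The sections that define and analyse the cue effect (Impact of cueing; Statistical analysis) name outcomes, change scores and tests, but no device: "A two-way mixed ANOVA will be used to assesses the effects of cueing modality and walk order on outcomes". The validation analysis is a separate item: "all gait characteristics derived from CuePD and reference will be compared using ICC" and Pearson correlation.

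**The concern.** If the cue-effect outcomes come from the app, both primary objectives use the same app data. Objective (i) asks whether CuePD measures gait validly in people with Parkinson's disease. Objective (ii) would assume that it does. The Statistical analysis section has no rule linking the two, so an outcome whose agreement is classed as poor (ICC below 0.5) would still enter the ANOVA or Friedman test unchanged.

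A small or absent effect on stride-time variability could then mean either that the cue does little or that the app's timing is too noisy to show it. That is the ambiguity the Abstract sets out to reduce. Stride-time variability is the most exposed outcome, because timing error adds directly to the dispersion being measured. A reference reading of the same strides is recorded at the same time but has no stated role in the cue analysis.

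**Working it through.** The plan gives no figure for app error, so there is nothing of its own to reproduce. The check has two parts: what the text implies about the source, and what app error would do under stated assumptions.

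**1. Source of the outcomes.** Three places bear on it. Reference standard says that validating the app makes the primary outcomes robust, which makes sense only if those outcomes come from the app. Validation of gait characteristics calls app validity essential for detecting change, which it would not be if Opal measured the change. The Discussion ties the cue-response measures to the phone on the lower back. Impact of cueing and Statistical analysis are silent. App dependence is therefore implied, not stated.

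**2. Stride-time SD.** Assumed: true SD falls from 25 to 20 ms (20%), with independent error of SD *e* at each foot contact. A stride time is the difference of two contacts, so observed SD = √(true² + 2e²).

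- e = 10 ms: √(625 + 200) = 28.7; √(400 + 200) = 24.5; fall 14.7%.
- e = 20 ms: √(625 + 800) = 37.7; √(400 + 800) = 34.6; fall 8.2%.

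On the plan's log-ratio scale (Equation 31, ignoring the small constant), assume CV falls from 3.0% to 2.5% while mean stride time falls from 1.1 to 1.0 s. The true log-ratio is ln(2.5/3.0) = −0.18. With error per stride of SD 10, 20 or 30 ms it becomes −0.15, −0.09 or −0.04.

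**3. Gait speed.** Simulated with assumed values: baseline mean 1.1 m/s (SD 0.2), true change 5% (SD 10%), zero-mean error added independently to each walk.

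| Error SD per walk (m/s) | Mean absolute change (m/s) | SRM of the difference | Mean % change (Equation 30) |
|---|---|---|---|
| 0 | 0.055 | 0.49 | 5.0 |
| 0.05 | 0.055 | 0.42 | 5.3 |
| 0.10 | 0.055 | 0.31 | 6.0 |

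The mean absolute change is unaffected. The standardised effect falls. The mean percentage change rises, because the noisy baseline is the denominator. Systematic error behaves differently again: reading 10% low throughout leaves the percentage change at 5.0%, while a constant offset of +0.1 m/s lowers it to 4.6%. Error that differs between cued and uncued walking could move the result either way.

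**4. Does a good ICC settle it?** Not by itself, because the ICC describes levels and the cue effect is a change. Read the ICC as the app's single-measure reliability, which holds without bias if both devices err equally; if all the disagreement is app error, the app's error is larger. With true between-walk correlation r, the reliability of the change score is

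R = 2(1 − r) / [2(1 − r) + 2(1 − ICC)/ICC].

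For ICC = 0.90 and an assumed r = 0.8: R = 0.4 / (0.4 + 0.222) = 0.643. An error-free SRM of 0.50 would then be observed as 0.50 × √0.643 = 0.40. An app at the lower edge of the plan's excellent band can still measure change noticeably less well than it measures level.

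**The case against.** **The source is inferred.** No sentence says the cue outcomes come from the app, and a condensed article may leave the device to the full protocol. The first part stands, and the point is worded accordingly. The second carries less weight: this article already fixes formulas, tests and alpha levels, and where it touches on the source it points to the app.

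**No contradiction with the Abstract.** A reader might infer that the plan breaks its own promise. It does not. The Abstract promises separate analyses that reduce ambiguity, and the plan has them: ICC and Pearson correlation for validation, ANOVA or Friedman for cue response. What is weakened is the aim, since separate analyses of the same app data do not fully serve it.

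**App error does not attenuate everything.** A reader might infer that it shrinks every cue effect. Step 3 shows otherwise for mean absolute and mean percentage change.

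**No power loss can be attached.** The sample-size section does not say whether its SRM of 0.5 is error-free or already includes measurement error. Degrading it could count the error twice, so no power figure is given.

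**Readers will see the agreement results, and variability will be read cautiously.** Both are true and help. Neither corrects a cue estimate, and agreement in level does not establish agreement in change (step 4).

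**App-derived response is a defensible target**, since the study also assesses CuePD as a retraining tool. That is a reason to report it, but not to leave the Opal readings out of the cue analysis.

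**Conclusion.** The point holds in this form: the device supplying the cue-effect outcomes is not fixed, the text implies CuePD, and the only stated use of the Opal data is validation. On that reading, primary objective (ii) depends on the open question of primary objective (i).

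Random app error would lower the SRM, Cohen's d, power and the CV stride-time log-ratio. It would leave the mean absolute change in gait speed and stride length unbiased and could inflate the mean percentage change. Differential error could bias in either direction.

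The size cannot be computed from the document. The fall of 14.7% to 8.2% in place of a true 20% rests on assumed stride-time SDs of 25 and 20 ms, an assumed contact error of 10 to 20 ms and independent errors. The gait-speed and ICC results likewise rest on assumed inputs.

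It would go too far to conclude that Opal outcomes make objective (ii) independent of the app. Under Smartphone and CuePD, the cue tempo is set from the participant's steps per minute plus 10%, and the app's own gait processing supplies that cadence. Poor app cadence would still alter the cue delivered, whichever sensor measures the response.

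**What to change.** In Impact of cueing and in Statistical analysis, state that gait speed, stride length, cadence and CV stride-time for the cue-effect analysis are computed from the Opal data for all walks. Report the app-derived cue effects alongside, with the app-minus-Opal difference in each estimated effect and its confidence interval. That difference also shows directly whether the app can detect change.

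If app-derived outcomes are to stay primary, the minimum is to say so and to pre-specify a repeat of the cue-effect analysis on the Opal data as a sensitivity analysis.

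The cost is wording and a little more analysis, since the sensors are already worn in each walking task. A rule is needed for walks with Opal failure. The change corrects outcome measurement only, not the dependence of cue tempo on app cadence, and the report should say so.

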#### Impact of cueing.

This examines the ability of different personalised auditory cues to modify/retrain gait in PwPD. By comparing the effects of metronome beats, instrumental music, and vocal music on gait speed, stride-time variability, and stride length, this outcome seeks to identify which auditory cues most effectively enhance gait stability and performance. ${\text{Coefficient of variance of stride}-\text{time }(\text{CV}}_{\text{stride}-\text{time}})$ will be calculated as the standardised measure of the dispersion of stride times. This provides a more reliable measure of stride-time variability and has shown to be a significant indicator of gait instability and an independent predictor of fall risk among older adults and PwPD, underscoring its importance in clinical and rehabilitative settings [73]. Measuring changes in gait will be key to assessing CuePD as a gait retraining tool.

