#### Walking/gait tasks.

Participants will choose from a selection of music tracks that span genres including pop, rock, R&B, and country. All walks will be 1-minute in duration in a continuous 25m loop, including two 8.5m straight segments and two 4m turns, Fig 3. Walk #1 will be at the participant’s natural walking pace to calculate a baseline cadence, i.e., a walk with no cueing (NC). Walks #2, #4, and #6 will be cued, with external auditory stimuli (BPM set at +10% of baseline cadence) which are metronome (Me), instrumental music (IM), and vocal music (VM). Participants will be assigned to one of three counterbalanced cue sequences for Walks #2, #4, and #6. For example, the first participant enrolled to the study follows Sequence 1, the second follows Sequence 2, the third follows Sequence 3, and the fourth cycles back to Sequence 1, etc.

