#### Adherence to cues and musicality.

Adherence will be treated both as a continuous variable (percentage change in cadence from baseline) and as a binary variable for group comparisons. The primary binary adherence definition is: adherent = ≥5% increase in cadence from baseline; non-adherent = < 5%. Mann–Whitney U tests will compare Gold-MSI between adherent and non-adherent participants. Participants with missing baseline or intervention-based cadence (e.g., wishing to withdraw or technology failure) will be excluded from binary adherence analyses and numbers excluded will be reported.

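### In the cueing analysis, stride-time CV alone cannot separate timing scatter from the tempo change that the +10% cue imposes

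*Protocol article*

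**What the plan says.** **The cue.** Under Walking/gait tasks, walks 2, 4 and 6 use "external auditory stimuli (BPM set at +10% of baseline cadence) which are metronome (Me), instrumental music (IM), and vocal music (VM"). The instruction for each cued walk is to step in time with the beat.

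**The outcome.** Under Impact of cueing, stride-time CV "will be calculated as the standardised measure of the dispersion of stride times", and it is justified as a marker of instability and fall risk. The section aims to find which cue best improves stability.

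**The analysis.** Under Statistical analysis: "A two-way mixed ANOVA will be used to assesses the effects of cueing modality and walk order on outcomes, i.e., cadence, gait speed, stride length," with stride-time CV as the fourth outcome. For CV, "change will be computed using the natural log-ratio of cue value to baseline" (Equation 31). On direction, "positive values imply an improvement for cadence, gait speed and stride length but negative is an improvement for CV" of stride time. Stride-time SD is not among the outcomes of the cueing model, and no allowance for the change in mean stride time is described.

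**Adherence.** The same section says: "The most effective cueing modality will be identified as the one producing a change closest to 10"%. The binary definition is "adherent = ≥5% increase in cadence from baseline; non-adherent = < 5"%. Gold-MSI scores are correlated both with adherence and with the CV log-ratio.

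**The concern.** CV is SD divided by the mean. The intervention acts on the mean by design: following the beat shortens stride time. The CV score therefore contains a term that reflects how far cadence moved, whatever happened to the regularity of stepping.

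Three readings are affected:

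- **Cue against baseline.** A rise in CV would be read as worse, although some or all of it may be tempo.
- **Cue against cue.** The cue followed most closely carries the largest tempo term, and a cue that nobody follows carries none. Cadence change closest to target counts as success on one criterion and pushes CV upwards on another.
- **Musicality.** Cadence change defines adherence and also enters the CV score arithmetically. The two sets of Gold-MSI correlations are therefore linked by construction.

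Reduced variability is part of a primary objective in the Introduction, and the Discussion singles out CV for its link with falls. The interpretation of this outcome therefore deserves care.

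**Working it through.** The protocol gives no expected value, SD or power for stride-time CV, so there is no figure of its own to reproduce. The check is algebra on the stated definitions.

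**Inputs from the protocol.** Cue target +10% of baseline cadence (Walking/gait tasks); binary adherence threshold +5% (Adherence to cues and musicality); Equation 31 (Statistical analysis).

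**Assumed inputs.** A +3% cadence increase, to represent a poorly followed cue. For the numerical example, stride-time SD 0.03 s and baseline cadence 105 or 120 steps/min. The CV ratio depends on neither the SD nor the baseline cadence.

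**Decomposition.** One stride is two steps, so mean stride time in seconds is 120/cadence. With cadence raised by a fraction c and the constant in Equation 31 negligible:

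change in log CV = ln(SD cue / SD baseline) − ln(mean cue / mean baseline) = ln(SD cue / SD baseline) + ln(1 + c)

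The second term is always present. What remains in the total depends on how SD responds to tempo. If SD is proportional to mean^b, the net shift is (1 − b) × ln(1 + c).

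| Cadence increase | SD unchanged (b = 0) | SD follows square root of mean (b = 0.5) | SD proportional to mean (b = 1) | Fall in SD needed for no change in CV, 1 − 1/(1 + c) |
|---|---|---|---|---|
| 3% | +0.030 | +0.015 | 0 | 2.9% |
| 5% | +0.049 | +0.024 | 0 | 4.8% |
| 10% | +0.095 | +0.048 | 0 | 9.1% |

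**Numerical example, SD fixed at 0.03 s.** Cadence 105 to 115.5: mean stride time 1.143 to 1.039 s, CV 2.63% to 2.89%. Cadence 120 to 132: mean 1.000 to 0.909 s, CV 3.00% to 3.30%. The ratio is 1.10 in both, and ln(1.10) = 0.095. Simulated one-minute walks (54 strides at 1.1 s against 60 at 1.0 s, both with SD 0.03 s) gave a mean log-ratio of +0.096.

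**Between cues.** If one cue is followed at +10% and another at +3%, with SD unchanged in both, their CV scores differ by 0.095 − 0.030 = 0.066 (unrounded terms) from the denominator alone.

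**The constant in Equation 31.** Its value is not given. With CV as a fraction between 0.02 and 0.05, a constant of 0.01 would shrink the 0.095 to between 0.065 and 0.080. A much smaller constant leaves it essentially unchanged.

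**The case against.** The strongest reply is that constant SD is not a neutral benchmark. CV is a conventional measure, chosen deliberately to express scatter relative to stride time. If SD shrinks in proportion to the mean, CV is undistorted, and SD alone would then credit a cue with a fall of 0.095 that is only tempo. This stands. It rules out calling CV the wrong measure or replacing it with SD. It also shows why one measure is not enough: the protocol does not say how SD responds to tempo, and CV alone cannot reveal it.

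A second reply is that the parts can be recovered, because log-SD change is log-CV change minus ln(1 + cadence change), and cadence is analysed too. That is true for each participant and makes the fix cheap. It does not work from separate group summaries, because the confidence interval needs the two changes paired within participant.

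A third reply is that the Discussion already asks for caution about variability, favours effect sizes over testing, and disclaims causal superiority of one cue. This limits the harm. But the stated reasons are dispersion and low power, not the denominator.

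Some stronger readings are tempting but not supported:

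- **That participants who follow the beat will be scored about 10% more variable.** This needs unchanged SD and full adherence.
- **That the ranking of cues will reverse.** The protocol gives no expected adherence by cue, and it names the most effective cue by cadence, not by CV.
- **That a false worsening will reach significance.** The protocol gives no SD for the log-ratio.
- **That CV is the study's only variability measure.** Validation of gait characteristics covers the variability of several others, for comparison with the reference device. The exploratory mention of stride-to-stride variability under Statistical analysis defines no further metric.

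**Conclusion.** The point holds for the cueing analysis. The Equation 31 score adds ln(1 + cadence increase) to the change in timing scatter, up to +0.095 when a participant fully follows the cue. The decomposition is exact when the added constant is negligible. The net shift depends on an unknown: all of the term remains if SD in seconds is unchanged, about half if SD follows the square root of the mean, and none if SD is proportional to the mean.

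A CV difference between cues, or a Gold-MSI correlation with CV change, therefore cannot by itself be attributed to timing scatter. The tempo term generally works against showing a benefit, so the risk is less a false claim of improvement than a misread rise in CV or a misread comparison between cues. The planned choice of CV is not an error; the weakness is interpreting it alone when the intervention sets its denominator.

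**What to change.** Keep stride-time CV as the planned outcome. Add the log-ratio of stride-time SD, which can be derived for every walk, to the same model. For each cue, report the log-ratios of SD, mean stride time and CV side by side, with estimates and 95% confidence intervals.

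State in advance that a rise in CV, or a CV difference between cues, without a corresponding change in SD will be described as possibly due to tempo, not as worsened stability. Apply the same caution to the Gold-MSI correlations with CV change.

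A rule that accepts a variability effect only when SD and CV move in the same direction is not advised. It has no threshold, and if SD is truly unchanged its estimate will still rise by chance about half the time.

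No new data, visits or participants are needed. The downside is small: one more reported exploratory outcome and a more guarded statement on variability.
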